### 3.0 STUDY PROCEDURES

#### 3.1. STUDY TEAM

This research will be undertaken by the Global Health Research Center of Central Asia (GHRCCA) at their regional office in Almaty, Kazakhstan. The GHRCCA was established in 2007 by Drs. [name], [name] and [name]. The Center focuses on emerging global health problems such as HIV, HCV, and other infectious diseases in Central Asia. GHRCCA’s main Central Asian office is in Almaty, Kazakhstan with satellite research offices in other Central Asian Republics. The Center uses rigorous social science and biomedical research to advance educational opportunities and help implement innovative public health policy solutions. This multi- disciplinary center creates crosscutting partnerships with governments, universities, business, and non- governmental organizations in Kazakhstan, the region, and worldwide to achieve its mission. The Center has built a strong infrastructure (well-trained researchers and superb media and technology systems) to allow for effective communication and shared data between the research teams in Central Asia and NYC. Ongoing training on guidelines to ensure confidentiality, security, and redundancy to avoid breaches in confidentiality and/or data loss are provided. Currently, in addition to the 22 staff, the Almaty office has a Community Collaborative Research Board and a number of faculty affiliates from Columbia University and universities in Kazakhstan, several pre- and postdoctorate students, and local and International NGO collaborators. GHRCCA has long worked with a number of local and international NGO’s in Kazakhstan and has developed successful relationships with NSPs including the ones recruited for the proposed study. Since 2004, we have built solid research collaboration with Kazakhstan’s Republican AIDS Center in Almaty and have established relationships with City AIDS Centers in Almaty, Karaganda, Temirtau, and Shymkent.

An organizational chart that describes the roles of GHRCCA staff and local staff is included in Appendix D.

#### 3.2. RELATIONSHIPS WITH LOCAL PARTNERS IN EACH CITY

As an implementation science study, BRIDGE is deeply dependent on local health service organizations and

oversight bodies for both project implementation and data collection. The thorough needs assessment process during the first year of the study, which included both mapping surveys and focus groups with PWID, provided the research team with an understanding of the system of HIV care in each of the four study sites where BRIDGE will be implemented. BRIDGE staff will work with local partners in both a formal capacity (through service contracts), and an informal advisory capacity.

#### *Service contracts:*

The BRIDGE study plans to sign the following work contracts:

Shymkent City AIDS Center: guaranteeing the support of the AIDS Center administrators in all project activities, hiring staff to conduct chart review for semi-annual reports, hiring staff to complete AppSheet tracking data, hiring nursing and outreach worker staff of all 8 trust points.

Karaganda City AIDS Center: (covers project activities in both Temirtau and Karaganda, as the Karaganda AIDS Center provides oversight for the Temirtau one) guaranteeing the support of the AIDS Center administrators in all project activities, hiring staff to conduct chart review for semi-annual reports, hiring staff to complete AppSheet tracking data, hiring nursing and outreach worker staff of all 8 trust points.

Service contracts will not be signed for Almaty City due to organizational preferences.

#### *Community Collaborative Research Board*

The CCRB for the proposed study will consist of representatives from TP clients, NGOs that serve PWID, police, AIDS centers, primary care clinics and opiate substitution therapy clinics (in cities where this service is available). We will have a CCRB in each city that will meet quarterly to focus on ensuring the contextual relevance of BRIDGE and study protocols.

### *3.3. RECRUITMENT AND INFORMED CONSENT*

#### PWID for BRIDGE Intervention Activities

As BRIDGE is an implementation study, recruitment for the BRIDGE intervention is conducted by the trust points under their normal scope of operations. Given the absence of personally identifiable data collected (the AppSheet system uses randomly assigned codes, and process measures will collect data in aggregate), we are requesting a waiver of documentation of consent for the HIV rapid testing and ARTAS components of the BRIDGE intervention, and a full waiver of informed consent for the SNS recruitment strategy. Below is a description of BRIDGE recruitment and intervention components that will be implemented in study sites over time.

The BRIDGE intervention, when it is rolled out in each study site, contains a recruitment component of peer-driven recruitment. This component is called the Social Network Strategy, and is being introduced in BRIDGE as part of a strategy for increasing the number of TP clients (see the BRIDGE Intervention Manual for more details)

We have successfully employed Social Network Strategy (SNS), a peer-driven recruitment approach, guided by network theory as a recruitment strategy in our prior studies with PWID in Central Asia. It has demonstrated effectiveness in reaching hidden and hard to reach populations of unknown HIV status and successfully linking them to HIV testing as well as re-engaging HIV-positive PWID who never initiated or were never retained in care. We clarify how we will be using peer-driven recruitment strategies below. Trust Point outreach workers will be trained to use SNS skills to teach clients to recruit 2-8 of their peers aged 18 or older. Each recruiter will receive 5-20 coded coupons and will be compensated \$2 for each peer who brings a coupon to the TP and completes HIV CTR. Coupons will contain the BRIDGE logo but not CU/GHRCCA logos or an IRB approval stamp in order to emphasize to potential clients that they are receiving services from a local Trust Point and not from a research organization (more details are provided below). Peer recruiters are asked to “register” their coupon numbers with the trust point nurse, complete a short informed consent procedure (see Peer Recruiter Consent Form) and answer a brief survey. More details on the coupon management procedures and peer recruiter survey are provided in a

separate protocol, in the peer recruiter consent form, and in the peer recruiter brief survey. Peer recruiters and clients will be apprised during informed consent that the BRIDGE Program is being run at trust points as part of a research study conducted by CU and GHRCCA (and that all program materials have received approval from the CU IRB). An electronic data system designed by the project will be used to track the number of returned coupons, recruitment links, and non-client referrals using the coupon management system. Senior TP outreach workers will identify the first set of peer recruiters, through internal TP participation or referral from TP clients or other agencies. Senior TP outreach workers will train peer recruiters to identify, screen, and invite other PWID in their social networks to participate in CTR services and become peer recruiters. Senior TP outreach workers will continue to engage peer recruiters and provide ongoing coaching and support about how they can approach and effectively engage their injecting network associates using culturally tailored messages that are designed for PWID who never initiated care, dropped out of care or were not considered for ART because their CD4 count was >350. Network associates who accept CTR services will be escorted to the TP, a nurse will provide CTR at the TP and then the network associate will be engaged as a potential recruiter for SNS.

The BRIDGE intervention manual describes the SNS recruitment strategy component of the intervention, where social networks are used to bring PWID into the trust points for testing. After this initial recruitment, it is the responsibility of the trust point nurse/social worker to engage clients in rapid testing and ARTAS, as set forth in the intervention manual. All PWID who receive rapid HIV testing under the BRIDGE intervention or participate in ARTAS case management sessions will undergo an informed consent procedure to acknowledge that de-identified data on services received will be provided to the BRIDGE study. This informed consent is described in more detail below. Clients of the trust point have the right to refuse to participate in all or individual BRIDGE activities.

#### AppSheet System

Starting in November 2016, the pre-implementation phase, trust points will begin to enroll clients in a barcode-based tracking system run through the program AppSheet. This program allows the research team to collect aggregate de-identified data on what services PWID receive during their regular visits to Trust Points and the AIDS Center.

All PWID receiving services during their regular visits will undergo an informed consent procedure to acknowledge that their data will be used as part of the BRIDGE study. We are requesting a waiver of documentation of consent for this portion of the study. As trust point services are provided anonymously, a written consent form would be the only document containing the participant's identifying information.

Participants will undergo a formal informed consent process, where they will be informed that by giving consent, they are releasing their information or data about services they receive at trust points and AIDS centers as part of the research study. The informed consent form details the data that will be collected [information about the services provided to them each time they come to the trust point or AIDS Center, such as the number of syringes given, tests received (including HIV rapid tests, STI tests, viral load, and CD4 count), participation in current and/or future programming (including rapid HIV testing and the ARTAS case management sessions in the BRIDGE intervention), and the other health care facilities they were referred to, such as polyclinics, NGOs, or TB centers.], and that all data will be de-identified prior to collection. Participants will be introduced to the AppSheet system, and all data collection procedures involving this system will be described to them in detail. The consent form will also detail all potential risks and benefits to the participant in agreeing to release their data to the BRIDGE study, and all measures to protect their confidentiality will be explained in detail.

The nurse will only proceed to enroll the client into the AppSheet system if the client provides verbal consent.

The first step in enrollment into the AppSheet system is the assignment of a barcode ID (referred to as the AppSheet ID) to each PWID who comes to the trust point to receive services. The trust point nurse will explain that this is a new electronic system for keeping trust point records. He or she will explain that this AppSheet ID is a randomly assigned code that will provide them with anonymous data every time clients visit the trust point and the AIDS Center. He or she will explain that only he or she will have access to the list that links their AppSheet code

with their pre-existing trust point UIC code (see AppSheet Protocol in Appendix A for a full description of this code), and that this list will be kept securely in a locked cabinet. Clients will be encouraged to bring their ID card with the barcode printed on it to each trust point or AIDS Center visit. We encourage and will provide support for trust point nurses to create documentation for client consent to use this code. The nurse will be given talking points to explain the AppSheet program to clients, and training to prepare him or her for situations in which a client may be reluctant to use the AppSheet ID, or may refuse to use it.

When the client brings this code to an appointment, the nurse will open up the AppSheet program on a computer provided by the BRIDGE staff, and scan the client's ID code to "check in" to the trust point or AIDS Center. The AppSheet program will then ask him or her to complete a short survey about the services received that day. The surveys are provided as attachments to this IRB protocol, and they ask about the services commonly provided under trust point and AIDS Center scopes of work, as determined by the BRIDGE study team during our mapping and needs assessment procedures. Once the BRIDGE intervention begins in each study site, trust point nurses will also be asked if they carried out BRIDGE intervention activities like ARTAS counselling sessions. Nurses as well as the BRIDGE study team will be able to see the anonymous data collected through this program.

Peer Recruiter Brief Surveys will also be conducted using AppSheet. Once the peer recruiter is oriented to the SNS portion of the BRIDGE Program and has been given his or her recruitment coupons, he will be asked to visit the trust point nurse to "register" his coupon code and exchange contact information with the nurse in order to receive compensation (see more details in the BRIDGE coupon protocol). At this time, the nurse will ask if the peer recruiter would be willing to complete a brief survey with some sociodemographic and risk information. If the peer recruiter agrees, she will administer informed consent, and if consent is provided, begin the brief survey. The peer recruiter is given the option to answer the survey questions on his own, once the nurse has logged him/her in using the coupon code.

### 3.4. PROCEDURES FOR EACH COMPONENT OF BRIDGE STUDY

#### *BRIDGE Intervention Procedures*

As described above, BRIDGE will be rolled out in 6-month intervals between study sites (Karaganda and Temirtau will implement BRIDGE at the same time). Trust points will implement the BRIDGE intervention with guidance and support from the BRIDGE study team. The BRIDGE study team will provide initial training (described below) and follow-up trainings.

BRIDGE trust points will recruit PWID for testing through the SNS recruitment strategies, provide rapid testing for HIV in accordance with existing trust point protocols and link those with reactive tests (or known positives who have fallen out of care) to HIV care at the AIDS Centers. The intervention involves several handouts and supplementary materials as described in the BRIDGE Program Manual. In order to promote Trust Point ownership of the intervention, and to decrease any potential negative associations with CU or GHRCCA (which is affiliated with CU) we are requesting to distribute a number of supplementary materials without CU or GHRCCA logos or IRB approval stamps. These materials include recruitment materials that will be distributed throughout the community, specifically: trust point staff BRIDGE business cards, release of information form for ARTAS referrals, appointment cards for ARTAS referrals to other service providers, rapid testing informational brochure, ART informational brochure, and rapid testing coupons.

As an implementation science intervention, BRIDGE trust points will control participant consent procedures, monitoring, and retention of participants. All Trust Point staff who implement the BRIDGE intervention receive human subjects protection training from GHRCCA staff. Trust points are governed by a number of existing regulations regarding patient privacy, and all trust point services are provided anonymously in Kazakhstan. The BRIDGE intervention materials and handouts are designed to allow flexibility for trust points to adhere to their regulations: materials refer to both clients and peer recruiters by ID codes rather than names, and clients are permitted to take part in all components of the BRIDGE program anonymously, as they are permitted to receive all trust point services anonymously. The Republican AIDS Center and Almaty City AIDS Center have reviewed all

BRIDGE intervention materials to ensure that they do not violate these regulations.

The Republican AIDS Center and the Almaty City AIDS Center have approved a release of information form that Trust Point nurses can use to provide referrals to ARTAS clients during the BRIDGE intervention. This form mirrors existing release of information forms used at the Trust Points, but is adapted to BRIDGE. This release form allows for an exchange of information between the Trust Point nurse and the medical professionals at referral organizations; it does NOT allow CU or GHRCCA staff to obtain information on ARTAS client referrals, and to avoid client confusion in this regard, we plan to distribute versions of this form which do not contain the CU IRB approval stamp.

### 3.5. ASSESSMENTS

In addition to the activities described above, BRIDGE will use a few additional assessment tools:

Semi-annual Reports from AC: The research team will request de-identified treatment records of all PWID served by each city's AIDS Center, in a report format prepared by AIDS Center staff twice per year. This allows the research team to compare HIV outcomes between those clients served by a BRIDGE trust point and those served by a non-BRIDGE trust point. For a detailed description of this data collection component, please see the Semi-Annual Report Protocol in Appendix B.

We are also requesting a waiver of informed consent for the Semi-Annual Report from the AIDS Center. As described in more detail in the Semi-Annual Report protocol in Appendix B, BRIDGE study team receive this data in report format once in 6 months, with all personal identifiers removed. The staff in charge of de-identifying this data are those who already have access to it by virtue of their job positions – epidemiologists and treatment specialists at the city AIDS Centers.

### 3.6. BRIDGE DATA COLLECTION

A summary of all sources of data collection is provided in the table below.

Table 2: BRIDGE Data Sources

| Name                    | Description & Purpose                                                         | Source                                                           | Identification of Data                                                                               | Pre-intervention         | Post-intervention                                                    |
|-------------------------|-------------------------------------------------------------------------------|------------------------------------------------------------------|------------------------------------------------------------------------------------------------------|--------------------------|----------------------------------------------------------------------|
| Process measures | Assess fidelity of BRIDGE implementation, for use in QA                       | Paper forms completed by BRIDGE TP nurses & OWs                  | Data identified by trust point, only aggregate data, no PHI or other sensitive information collected | n/a (not collected)      | Forms completed, collected and reviewed monthly by site coordinators |
| CFIR Surveys     | Assess implementation climate & organizational culture of BRIDGE trust points | TP, AC and RAC staff who are involved in the BRIDGE intervention | Data identified by study-assigned ID code                                                            | Every 6 months           | Every 6 months                                                       |
| AppSheet System  | Short surveys to assess services                                              | Filled out by TP and AC                                          | All PWID clients given                                                                               | Continuous collection of | Continuous collection of                                             |

|                   |                                                                                        |                                                                     |                                                                                                                                                                                                                                                   |                                                                                                    |                                                                                                                      |
|-------------------|----------------------------------------------------------------------------------------|---------------------------------------------------------------------|---------------------------------------------------------------------------------------------------------------------------------------------------------------------------------------------------------------------------------------------------|----------------------------------------------------------------------------------------------------|----------------------------------------------------------------------------------------------------------------------|
|                   | received at each AC/BRIDGE TP and brief information on peer recruiters                 | nurses during each patient visit or at initial peer recruiter visit | random ID number (in barcode code form). All data on program level participants is de-identified and available only in aggregate form. Peer recruiters are entered into the system using the anonymous bar code on their coupons for distribution | data (pre-implementation surveys, which contain no questions about BRIDGE intervention components) | data (post-implementation surveys, which contain additional questions about BRIDGE intervention components received) |
| AC Reports | Excel-based report on biological testing & ART regimes for all HIV+ PWID in study site | Completed by epidemiological staff at AC                            | Data is de-identified by AC staff before GHRCCA staff are given access                                                                                                                                                                            | Report is sent to GHRCCA in Kazakhstan once every 6 months                                         | Once every 6 months                                                                                                  |

### 3.7. TRUST POINT ELIGIBILITY CRITERIA & SELECTION

Bridge will be carried out at a total of 24 trust points, or 8 per site (3 from Temirtau and 5 from Karaganda will be considered one site). A selection process within each site will identify the “BRIDGE Trust Points” who will carry out the intervention, and the “non-BRIDGE Trust Points” where no intervention will take place.

A multistage site selection process was carried out according to Figure 5:

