### 3.8. PARTICIPANTS

#### Categories of Participants for this study

There are three categories of participants in this implementation study:

- 1) PWID Program Participants: - All PWID (regardless of HIV status) in each of the four cities are considered participants in terms of program-level outcomes of BRIDGE. These clients are eligible to receive various components of the BRIDGE intervention: they may be recruited by peer recruiters as part of the SNS strategy or may be peer recruiters themselves, they will receive CTR at trust points, and those who are HIV-positive are eligible to participate in ARTAS.

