### **PURPOSE OF APPSHEET DATA COLLECTION**

The purpose of AppSheet data collection is to collect **de-identified** aggregate-level data on services received by PWID at BRIDGE trust points and city AIDS Centers in each of our four study sites.

The data provided in this tracking system will be used to test the hypotheses of Study Aims 1 and 2. Study Aim 1 seeks to evaluate the effectiveness of implementing BRIDGE's enhanced service integration approach in Trust Points (TPs) on linking HIV-positive People who Inject Drugs (PWID) to HIV care. Study Aim 2 seeks to evaluate the effectiveness of BRIDGE's enhanced service integration approach on increasing HIV testing in TPs and increasing retention in HIV Care Clinics. This tracking system allows us to monitor "linkage" to care and repeated testing visits among PWID by tracking what services PWID receive.

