## **ID NUMBERS**

ID numbers are assigned by the nurses at BRIDGE trust points. Starting in November 2016, trust point nurses in BRIDGE trust points will begin to assign unique 6-digit ID codes to their regular PWID clients. The 6-digit code will consist of the following components:

Digits 1-3: code of the trust point where the ID is being assigned

Digits 4-6: random digits (we suggest 001, 002, 003, etc.)

The nurse will be responsible for keeping a list of all ID codes assigned. Trust point services in Kazakhstan are anonymous, and in regular operations, nurses track clients using a standardized “unique identification code” or UIC. The nurses at BRIDGE trust points must keep a master list of BRIDGE study codes and UICs. If a client should lose their ID card (described below), the nurse can check this record and provide him with a new one based on his/her UIC.

This ID number will be converted into a scan-able bar code format and printed on a small laminated ID card that can be attached to the client’s keychain.

This bar code can be scanned by a tablet or smartphone within an AppSheet survey, saving time and reducing the change of error. The keychain format is intended to prevent loss of the ID card.

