## INDICATORS PROVIDED IN REPORT

Semi-annual reports shall contain following indicators:

- BRIDGE ID (as index)
- Age
- Sex
- Date when client's HIV-positive status was confirmed
- Name of the trust point where client has received services in the past 6 months
- Date registered as client of the AIDS Center
- Was the client given a CD4 test in the past 6 months?
  - Test system used for CD4
  - Results of CD4 test
- Was the client given a Viral Load test in the past 6 months?
  - Test system used for Viral Load
  - Results of Viral Load test
- Clinical Stage of Disease in the past 6 months
- Has the client begun ART?
  - Date when the client begun ART
  - Name of ART drugs (regimens)
- Changes in the client's ART regime in the past 6 months
- Changes in the specific ART medications in the past 6 months
- Testing for STIs at the AIDS Center in the past 6 months
  - STIs diagnosis in the past 6 months (if available)
  - Treatment for STIs (if available)
- Registration at the drug treatment clinic

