## Data Analysis Plan for Primary Study Aim

### Hypothesis:

Compared to pre-implementation time blocks, time blocks where Bridge is implemented will have increased numbers of PWID clients who (a) attend NSPs, (b) receive a rapid test for HIV at NSPs, and (c) link to HIV care at the AIDS center, when their test is positive for HIV care in the past 6 months)

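### Primary counts are taken through BRIDGE trust points only, so a client who moves from a non-BRIDGE trust point in the same city is scored as a gain

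*Combined protocol and SAP*

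**What the plan says.** **Where BRIDGE runs.** Section 3.7: "Bridge will be carried out at a total of 24 trust points, or 8 per site". The same section provides for non-BRIDGE TPs in each site, "where no intervention will take place". Section 2.2 instead says that every TP site in a city gets BRIDGE at one time. It calls contamination minimal because the cities are far apart.

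**Where the primary data come from.** Appendix A says that AppSheet collects "data on services received by PWID at BRIDGE trust points and city AIDS Centers". On enrolment it adds: "ID numbers are assigned by the nurses at BRIDGE trust points". Table 2 lists no attendance or testing data from non-BRIDGE TPs.

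**What is tested.** The Data Analysis Plan for the Primary Study Aim states that BRIDGE time blocks "will have increased numbers of PWID clients who (a) attend NSPs, (b) receive a rapid test for HIV at NSPs", and link to HIV care when positive. The test is a difference in means, before against during implementation, over the 24 TPs. Table 1 gives linkage as both a number and a percentage of HIV-positive clients.

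**Who may be recruited.** Section 3.3 pays a recruiter $2 for each peer who redeems a coupon and completes testing. Section 5.1 describes no formal screening. No rule in the documents bars or flags a peer already served at another TP.

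**Who the trial is about.** Section 3.8: "All PWID (regardless of HIV status) in each of the four cities are considered participants in terms of program-level outcomes of BRIDGE".

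**The concern.** The programme-level population is all PWID in the four cities, but the primary counts see only those who pass through a BRIDGE TP. If a coupon brings in someone who would otherwise have attended and been tested at a non-BRIDGE TP nearby, the BRIDGE TP records one more client and one more test. The loss at the other TP is not in the primary data.

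Movement of this kind begins when coupons begin, that is, at rollout, so it has the same timing as a true effect. Comparison with cities not yet started does not remove it. Neither do the permutation test or the mixed-model and GEE analyses. Section 2.2 considers spread between cities, not movement within one.

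What is at stake is the wording of the conclusion. More clients at BRIDGE TPs could be reported as more PWID reached, tested and linked, and so used to support the scale-up planned in Section 10.3, when part of the rise is a change of venue.

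**Working it through.** **1. The base.** Section 5 gives 597 registered clients per TP and a pool of 14,328 at the study TPs. 24 × 597 = 14,328, which reproduces exactly. The same section puts 25,394 PWID in the four cities, so 25,394 − 14,328 = 11,066 (43.6%) are outside this pool. How many of them use non-BRIDGE TPs is not stated.

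**2. Non-selected TPs that the documents list (Section 3.7).**

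- Criterion 1, more than 20 km from an AIDS Center: Almaty 1, Shymkent 8, Karaganda/Temirtau 3. Total 12.
- Criterion 2, no on-site rapid testing: Karaganda 1. (Two Almaty TPs also fail it but are kept.)
- Criterion 3, no private room: Karaganda 1, Shymkent 1.

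That is 12 + 3 = 15 if none is counted twice. Almaty TPs ranked below the top eight, and any removed under Criteria 4 and 5, are not counted in the text.

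**3. Attendance and testing.** Let k be the number of non-BRIDGE TPs and d the share of their clients who move. With no net change in the city:

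apparent rise = d × k × 597 / 14,328

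The values of d, and the use of 597 for these TPs, are assumptions.

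| k | Clients (k × 597) | d = 10% | d = 25% |
|---|---|---|---|
| 3 (not excluded for distance) | 1,791 | 179 movers, 1.2% | 448 movers, 3.1% |
| 15 (all listed) | 8,955 | 896 movers, 6.3% | 2,239 movers, 15.6% |

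If non-BRIDGE counts were added to the outcome, every cell would be 0%.

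**4. Plausibility of the upper row.** (24 + 15) × 597 = 23,283, and 23,283 / 25,394 = 92% of all PWID in the four cities would be registered at a TP. So 597 is probably too high for the TPs left out.

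**5. Linkage.** AIDS Center visits are recorded too, but through an ID that only BRIDGE TPs issue. Assume that one third of a TP's HIV-positive clients are linked, that movers equal 10% of that TP's own HIV-positive clients, and that a share c of movers is already in care.

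- Rise in the linked count = 0.10 × c / 0.333
- Linked percentage = (0.333 + 0.10 × c) / 1.10

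| c | Rise in linked count | Linked percentage (from 33.3%) |
|---|---|---|
| 33.3% | 10% | 33.3% |
| 60% | 18% | 35.7% |
| 90% | 27% | 38.5% |

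The count rises whenever any mover is already in care. The percentage moves only if movers differ from the TP's existing clients.

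**The case against.** **Few clients may move.** Twelve of the 15 listed TPs were left out for distance, and Section 3.7 itself treats transport as a large barrier. The $2 goes to the recruiter; Section 3.7's companion text on compensation (Section 3.8) gives the tested peer nothing. Recruitment messages in Section 3.3 are aimed at people who never started or dropped out of care. This stands as an argument about size. It does not settle it: the 20 km is measured to the AIDS Center, not to the nearest BRIDGE TP, and the unselected Almaty TPs are not counted.

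**Some movers are real gains.** A client from a TP without rapid testing who is then tested at a BRIDGE TP is a true increase in testing. This stands.

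**Part of the loss is visible.** The AIDS Center report covers all HIV-positive PWID served and names the TP used in the past six months, and Appendix B plans a BRIDGE against non-BRIDGE comparison. This stands for HIV-positive PWID, but that report is assigned to Aim 2 and says nothing about attendance or testing.

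**Prior TP use may be recorded elsewhere.** Section 3.3 mentions tracking of non-client referrals and a separate coupon protocol, which is not in the documents. It may help, but the analysis plan gives it no role.

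**Section 2.2 may mean only the study's TPs.** That is possible, since Sections 3.7 and 5 use TP sites in that sense. A clarifying phrase would then be enough.

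**Conclusion.** The point holds for the counts. The primary data score within-city movement as an increase, and nothing in the primary analysis offsets it.

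The size is not known. The three listed TPs not excluded for distance give about 1% to 3% of the base at an assumed 10% to 25% redirection. A reader might infer a bias of 6% to 16% from all 15. The documents do not support that as an expected size, because 12 of the 15 are distant and the calculation needs 597 clients at every TP.

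A reader might also infer that displacement alone could satisfy every primary measure. That is not so for the linked percentage, which needs movers to differ in care status. Nor do the documents show that displacement occurs. They show that the plan could not detect it in attendance and testing.

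The defect limits what may be concluded about the city. It does not invalidate the comparison at BRIDGE TPs.

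**What to change.** 1. Keep the TP-level primary test.
2. Pre-specify a city-wide supporting analysis from the AIDS Center report, whatever TP is named, covering: PWID newly confirmed HIV-positive; PWID newly registered, using the field "Date registered as client of the AIDS Center"; and all HIV-positive PWID with a CD4 or viral load test in the past six months. The last is needed because BRIDGE also re-links known positives (Section 3.4), and the listed indicators contain no visit dates. Show the BRIDGE against non-BRIDGE split over time.
3. For attendance and testing, ask the Republican AIDS Center, which regulates all TPs, for aggregate client and rapid-test totals at non-BRIDGE TPs in the same cities, if they exist. Report the net city total.
4. State in advance that, if the city-wide counts do not rise, the conclusion will be an increase at BRIDGE TPs, not an increase in PWID reached, tested or linked in the city. Do not make the city-wide count a pass/fail condition.
5. Reconcile Section 2.2 with Section 3.7 on whether all TPs in a city receive BRIDGE.

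**Cost.** No new participants. Item 2 uses data already planned every six months from November 2016 to May 2020. Item 3 is one recurring aggregate request, and the documents do not say whether such totals are kept. The drawback is dilution: 43.6% of the cities' PWID lie outside the BRIDGE pool, so a true effect will look smaller city-wide. The city-wide counts therefore support the primary test and do not replace it.
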